**Trial / Study Statistician:** **[name] [name]**

Professor in Genetic and Molecular Epidemiology

Surgery, Trauma and MSK Ageing

Nottingham Biomedical Research Centre,

University of Nottingham, [name]

[name]

**Trial / Study Coordinating Centre:** Nottingham Digestive Diseases Centre,

University of Nottingham, Queens Medical Centre,

[name]

SYNOPSIS

| Title | The Effect of Pectin Supplementation on Patients with Metabolic Dysfunction-Associated Steatotic Liver Disease (MASLD): A Randomised Placebo-Controlled Dietary Intervention Study |
| --- | --- |
| Acronym | PEC-MASLD |
| Short title | Pectin Supplementation and MASLD |
| Chief Investigator | [name] [name] |
| Objectives | To investigate the effects of daily pectin supplementation ingestion on pathways promoting systematic inflammation with metabolic dysfunction-associated steatotic liver disease (MASLD) enabling a better understanding of the mechanisms of action. This includes effects on gut microbiome composition, body weight, lipid metabolism, and gut and liver physiology. |
| Trial Configuration | Single centre placebo controlled randomised dietary intervention study |
| Setting | Identification of participants from secondary care setting for research across research centres: Nottingham Digestive Diseases Centre, University of Nottingham; Nottingham Clinical Research Facility at Nottingham University Hospitals NHS Trust; and Sir Peter Mansfield Imaging centre |
| Sample size estimate | The sample size was calculated using Raosoft® calculator with Confidence level of 95% ± 5% and response distribution of (50%) to know the minimum sample size. The total sample size came out to be 14 per arm. The sample size of this study is equal to 15 per arm to obtain the statistical power for the study.  This calculation was based on a previous pectin pilot study which found significant differences in 4 inflammatory markers with n=14 healthy adult volunteers. |
| Number of participants | 45 |
| Eligibility criteria | **Inclusion criteria for the main study:**  -Patients with clinical diagnosis of MASLD (formerly termed non-alcoholic fatty liver disease (NAFLD)), having assessment suggesting that liver fat > 5% (e.g. histological evidence or/ and Transient Elastography using Controlled Attenuation Parameter (CAP)- FibroScan™ in the past month and/or liver imaging (such as ultrasound, computerized tomography (CT) or magnetic resonance imaging (MRI)).  -Participants willing and able to give informed consent for participation in the study.  -Participants aged ≥18 years who have a body mass index (BMI) between 18.5 and 39.9 kg/m^2^ and stable weight (weight gain or loss ≤ 3kg) for the past 3 months.  -For diabetic participants: controlled blood glucose levels Haemoglobin A1C (HbA1c) <7.0% (<53 mmol/mol) [1].  -Able to undergo CAP-FibroScan™.  **Inclusion criteria for healthy participants who will have MRI scans:**  -Participants willing and able to give informed consent for participation in the study.  -Participants aged ≥18 years.  - participants with CAP<250 kpa<8kP by a FibroScan™ within the past 6 months.  **Exclusion criteria for the main study:**  -Have allergy toward soya, milk or chocolate.  -Have allergy toward pectin.  -Participants on vegan diet.  -Have eating disorders or difficulties or gastrointestinal conditions e.g. malabsorptive conditions such as coeliac, Irritable Bowel Syndrome (IBS) or Inflammatory Bowel Disease (IBD) or gastroparesis.  -Have chronic malnutrition condition.  -History of major surgery which potentially limits participation or completion of the study.  -History of previous intestinal surgery known to affect food intake  or digestive function, including bariatric surgery.  -Use of antibiotics, antifungal medications, probiotics or prebiotics 90 days before the start of the study.  -Are taking the following medications: immunosuppressants, amiodarone and/or perhexiline.  -Are currently following or anticipated to commence a specialised commercially available weight loss diet and/or program or concomitant use of any weight loss medication or herbal weight loss products.  -History of side effects towards probiotics or prebiotics.  -History or current psychiatric illness.  -History or current neurological condition (e.g. epilepsy).  -Participants with other liver abnormalities.  -Evidence of monogenic metabolism diseases such as Lysosomal acid lipase deficiency (LALD), Wilson disease, Hypobetalipoproteinemia, or inborn errors of metabolism.  -Have had a weight change exceeding 3 kg within 3 months.  -Uncontrolled diabetes, active malignancy, or chronic infections.  -Having symptoms of active infection.  - Excessive alcohol intake defined as self-reported intakes greater than 21 units per week in men, and 14 units per week in women.  -Participants who are pregnant, breast feeding or actively planning pregnancy will be excluded from the study.  -Participation in any other trial in the last 3 months.  **Exclusion criteria for healthy volunteers MRI scans and patients optional MRI scans:**  -Contraindications for MRI scanning: having pacemakers, defibrillators, neurostimulators, prohibited medical implants, and foreign bodies (e.g. bullets, shrapnel, metal slivers), history of metallic foreign body in eye(s) and penetrating eye injury that could present a risk during an MRI scan.  -Difficulty breathing or inability to lie flat, as well as conditions that could worsen under stress (such as anxiety or panic disorders, claustrophobia, uncontrolled hypertension, or seizure disorders) severe enough to prevent undergoing an MRI.  -Contraindications to Hyoscine butylbromide (Buscopan®): Previous adverse drug reaction (allergic, hypersensitivity or other), Angle-closure glaucoma, tachycardia, ischaemic heart disease, myasthenia gravis, prostatic enlargement with urinary retention requiring catheterisation, mechanical stenosis in the gastrointestinal tract, paralytic or obstructive ileus, hypotension, cardiac disease, recent heart attack or any arrhythmias, thyrotoxicosis, gastro-oesophageal reflux disease, hiatus hernia, ulcerative colitis. |
| Description of interventions | Arm A: Pectin fibre (15g/day) combined with 15g whey protein supplement and 5g cocoa powder reconstituted as a shake Arm B (control/placebo): Whey protein supplement (30g/day) and 5g cocoa powder reconstituted as a shake.  To validate MRI scans as a tool to assess intestinal wall thickness to indicate gut permeability on MASLD patients, our team will scan 15 healthy volunteers twice, at baseline and after 6 weeks, and then compare their results with MASLD participant results at baseline and after 6 weeks. |
| Duration of study | Duration of the study:  24 months.  Duration per participant:  Each participant will participate for 6 weeks. |
| Randomisation and blinding | The study will be a parallel design, placebo-controlled, randomised dietary intervention study in which each participant will be randomly assigned to either pectin supplementation or control dietary supplement using online software (sealedenvelope.com). |
| Outcome measures | Primary outcomes:  Quantification of blood markers associated with physiological processes and pathways contributing to systemic inflammation pathway (TNFα, IL-6, IL-10, IFNᵞ, C-Reactive Protein, Zonulin (Haptoglobulin), IL-1β).  Secondary outcomes:   1. Assessment of changes in anthropometric measures 2. Assessment of changes in general metabolic indicators, such as fasting blood glucose and other blood-based markers relevant to MASLD (e.g., CK18-M30, CK18-M65, PROC3, Enhanced Liver Fibrosis (ELF), NIS2+™, YKL-40, microRNA miR-34a-5p, liver-associated enzymes such as Alanine Aminotransferase (ALT), Aspartate Aminotransferase (AST), gamma-glutamyl transferase (GGT), Alkaline Phosphatase (ALP)), bilirubin levels, lipid profiles, and platelet counts. 3. Exploration of modifications in non-invasive physiological assessments linked to liver characteristics, such as fat content and stiffness through controlled attenuation parameter (CAP) and transient elastography. 4. Observation of alteration in fat in liver and other surrounding abdominal organs through Dixon MRI sequence in patients who will agree to have 2 MRI scans. 5. Validation of MRI measures (T2*) as a tool to measure gut permeability among MASLD patients and investigation of changes in gut permeability in participants undergoing two MRI scans. 6. Investigation the presence of gene variants such as MUC2, encoding Mucin protein, that are associated with gut permeability. |
| Statistical methods | Data input, cleaning and analysis will be conducted using a statistical software such as PRISM or SPSS (IBM Corp, Armonk, New York) or R software (R Foundation for Statistical Computing, Vienna, Austria). Descriptive statistics will be reported as means ± standard deviations (SD) or medians with interquartile ranges (IQR) for continuous variables, and as frequencies and percentages for categorical variables. Prior to analysis, data will be checked for normality using the Shapiro-Wilk test. Standard parametric and non-parametric tests (where assumptions of normality are violated) will be used to assess significance of changes compared to baseline on both pectin arm and placebo arm. Mixed-effects linear regression models will be used to assess the intervention effect of pectin compared to placebo, adjusting for baseline values and relevant covariates such as age, sex, ethnicity and BMI. The interaction between time (baseline and follow-up) and group (pectin vs placebo) will be examined to determine if the changes over time differ between the two groups. P-value < 0.05 will be considered statistically significant for all analyses. |

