**Protein Powder**

Whey protein

Contains: Whey protein isolate (milk) (100%), Emulsifier (Soya Lecithin, Sunflower Lecithin)

Per 100g of whey protein: Fat 0.9g, of which saturates 0.4g, Carbohydrate 2.8g, of which sugars 1.7g, Salt 0.68g, 86g Protein

Appearance: White powder

Solubility: Soluble in Water

Stability: Stable under normal shipping and handling conditions

Usual Daily Dose: 20-30g

Storage: Store at room temperature in cool and dry place away from sunlight.

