**Protein Powder**

Whey protein

Contains: Whey protein isolate (milk) (100%), Emulsifier (Soya Lecithin, Sunflower Lecithin)

Per 100g of whey protein: Fat 0.9g, of which saturates 0.4g, Carbohydrate 2.8g, of which sugars 1.7g, Salt 0.68g, 86g Protein

Appearance: White powder

Solubility: Soluble in Water

Stability: Stable under normal shipping and handling conditions

Usual Daily Dose: 20-30g

Storage: Store at room temperature in cool and dry place away from sunlight

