**Packaging and labelling**

The study team will repackage the powders into zip lock bags labelled only as the study arm A or B based on a local SOP that was written by the study team. The repackage process will take place at a clean room at School of Medicine, University of Nottingham, E-Floor by a food hygiene trained researcher. The researcher will use electronic food scale to weigh the powders. All prepared zip bags will be kept in a dry secure location. This will be in a locked cabinet in [name] and only accessible by designated study researchers. Participants will be provided the supplements mixed with the flavour in clear plastic food safe zip lock bags. Each bag will contain either 15g of pectin with 5g of cocoa powder and 15g of whey protein powder or 30g of whey protein powder with 5g of cocoa powder.

Participants will be advised to pour 250 ml of water into a shaker bottle, then empty the whole powder inside the bag and shake the bottle until they have consistent shake. They will be advised to add water up to 50 ml if required to enhance solubility. Participants will be advised to consume one bag per day, each participant will be given 42 zip bags to be consumed within 42 days. A brochure with easy instructions will be given to each participant.

Participants will be advised to take the intervention in the morning. If they forget to take it in the morning, they will be advised to take it once they remember. Moreover, participants will be advised to avoid missing doses or overdoses as much as they can and to report missing doses or overdoses incident to the study team if that will happen. They will be given a tracker to track their daily study supplement consumption.

The study team will use pectin that is provided from BOC SCIENCES INC, United States similar to the pectin that was used on the healthy volunteer study that was previously conducted at the University of Nottingham [31].

Mannitol 2.5% / Locust bean gum 0.2% will be used as an oral contrast during u scans. It will be an oral solution that will be prepared by the MRI research team on the MRI visit day. Each drink will contain 25g of Mannitol and 2g of Locust bean gum that will be dissolved in 1000 ml of water.

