**Dietary intervention (6 weeks):**

Control and intervention arms: Each participant will be randomly assigned to either pectin with whey protein and cocoa powder or control whey protein with cocoa powder using online software (sealedenvelope.com) to determine intervention A or B at enrolment. Randomisation will ensure equal distribution of key characteristics that might confound between-group comparisons and will be evaluated using baseline data analysis. Participants in the intervention arm (N=15) will be required to take 15g of pectin combined with 15g of unflavoured whey protein powder and 5g of cocoa powder as a flavour per day for a period of 6 weeks. The participants in the placebo/control arm (N=15) will be required to take 30g of unflavoured whey protein powder combined with 5g of cocoa powder as a flavour per day for the same period of 6 weeks. All supplements will be provided, pre-weighed, in food grade pouches and will be given sufficient cover the total intake for the 6-weeks period. Participants will be asked to incorporate the supplement provided in 250-300ml of water taken once at morning or evening. Regular weekly contact will be made via phone calls by [name] to record patients’ feedback or any adverse event that might occur due to ingestion of supplements and to ensure participants receive any information that becomes available during the course of the research that may be relevant to their continued participation .

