# STATISTICS

### Methods

The data will be analysed by [name] on-site at the University of Nottingham under supervision of the CI, co-investigators and NIHR Nottingham Biomedical Research Centre liver/GI statistical team.

All analyses will be conducted on password-protected University of Nottingham computers or University of Nottingham laptops, that are backed up to cloud servers.

Data input, cleaning and analysis will be conducted using a statistical software such as PRISM or SPSS (IBM Corp, Armonk, New York) or R software (R Foundation for Statistical Computing, Vienna, Austria). Descriptive statistics will be reported as means ± standard deviations (SD) or medians with interquartile ranges (IQR) for continuous variables, and as frequencies and percentages for categorical variables. Prior to analysis, data will be checked for normality using the Shapiro-Wilk test. Standard parametric and non-parametric tests (where assumptions of normality are violated) will be used to assess significance of changes compared to baseline Characteristics of participants, outcome measures at baseline (symptoms, clinical parameters) and post-intervention will be summarized by intervention group using descriptive statistics. The differences between the two groups will be tested by matched-pair Student’s t-test. Data will be presented as mean± standard deviation and the significance of difference will be set at p <0.05.

Mixed-effects linear regression models will be used to assess the intervention effect of pectin compared to placebo, adjusting for baseline values and relevant covariates such as age, sex, ethnicity and BMI. The interaction between time (baseline and follow-up) and group (pectin vs placebo) will be examined to determine if the changes over time differ between the two groups.

Any changes in the planned statistical methods will be documented in the study report.

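### The control bag holds twice the whey of the pectin bag, so the between-arm contrast is pectin in place of an equal weight of whey, not pectin against a placebo

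*Protocol*

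**What the plan says.** The Synopsis (Description of interventions) defines the pectin arm as "Arm A: Pectin fibre (15g/day) combined with 15g whey protein supplement and 5g cocoa powder reconstituted as a shake" and the comparator as "Arm B (control/placebo): Whey protein supplement (30g/day) and 5g cocoa powder reconstituted as a shake". Two later sections repeat these amounts. Packaging and labelling has each bag holding "15g of pectin with 5g of cocoa powder and 15g of whey protein powder or 30g of whey protein powder", with 5 g of cocoa in both. Dietary intervention (6 weeks) gives the control arm "30g of unflavoured whey protein powder combined with 5g of cocoa powder as a flavour per day for the same period of 6 weeks".

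Details of Product(s) lists the same whey isolate for both arms, with this label: "Per 100g of whey protein: Fat 0.9g, of which saturates 0.4g, Carbohydrate 2.8g, of which sugars 1.7g, Salt 0.68g, 86g Protein". Packaging and labelling provides 42 bags per participant, one a day.

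The title calls the study placebo-controlled and says that it concerns the effect of pectin. Purpose and Primary Objective also frame the question as what pectin does. Statistics, Methods, turns this into an analysis: "Mixed-effects linear regression models will be used to assess the intervention effect of pectin compared to placebo". That model adjusts for baseline values, age, sex, ethnicity and BMI, and includes a time-by-group interaction. The Synopsis (Statistical methods) says the same.

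**The concern.** A placebo comparison supports a statement about one ingredient when the arms differ in that ingredient alone, or when whatever replaces it does nothing to the outcomes. Here the arms differ in two ingredients: the pectin arm has 15 g more pectin and 15 g less whey. Whey is a protein supplement, and the protocol never says that it is inert for the endpoints or that the comparison is a substitution.

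What is at stake is how the result is attributed. The primary endpoint is a set of inflammatory markers. The secondary endpoints include BMI, fasting glucose, lipids, gut microbiome and the FibroScan CAP value. For each, the plan would report as an effect of pectin a difference that also contains the effect of a smaller whey intake.

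**Working it through.** The protocol gives no figure for this contrast, so there is none to reproduce. The check uses the stated bag contents and the product label.

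**Inputs**
- Arm A, per day: 15 g pectin, 15 g whey, 5 g cocoa (Synopsis; Packaging and labelling; Dietary intervention).
- Arm B, per day: 30 g whey, 5 g cocoa (same three places).
- Protein content of the whey: 86 g per 100 g (Details of Product(s), Protein Powder, both arms).
- Number of bags: 42 (Packaging and labelling).

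**Step 1: bag weight.** Arm A: 15 + 15 + 5 = 35 g. Arm B: 30 + 5 = 35 g. The bags match on weight.

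**Step 2: whey.** 30 / 15 = 2, so arm B has twice the whey. The gap is 30 − 15 = 15 g a day, and 15 × 42 = 630 g over the intervention.

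**Step 3: protein from whey.** Arm A: 15 × 0.86 = 12.9 g a day. Arm B: 30 × 0.86 = 25.8 g a day. The gap is 25.8 − 12.9 = 12.9 g a day, and 12.9 × 42 = 541.8 g, about 542 g, if every bag is taken.

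**Step 4: what the contrast estimates.** Write Y(p, w) for the mean outcome under p g of pectin and w g of whey, with cocoa the same in both arms. Then

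Y(15, 15) − Y(0, 30) = [Y(15, 15) − Y(0, 15)] − [Y(0, 30) − Y(0, 15)].

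The first bracket is the effect of 15 g pectin on a background of 15 g whey. The second is the effect of a further 15 g whey. The identity is exact and does not need the two ingredients to act additively. The contrast equals the first bracket only if the second is zero.

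**Step 5: whether an analysis can separate them.** Every participant is assigned either (15, 15) or (0, 30). Across arms, pectin dose and whey dose have correlation −1. A design matrix with an intercept, pectin dose and whey dose has rank 2 for 3 parameters. Baseline values, age, sex, ethnicity and BMI carry no information about assigned whey dose within an arm, so adjusting for them leaves the rank problem in place. The time-by-group interaction carries the same combined contrast. Change from baseline within arm A does not isolate pectin either, because that arm also takes whey and cocoa.

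**The case against.** The strongest reply is that a weight-matched food comparator is a legitimate design and that any filler makes the comparison a substitution. If whey were equalised and the control bag made up with something else, pectin and that filler would again be perfectly confounded with arm. This stands. It means that changing the bags is a trade-off rather than a clear correction, and bag content is for the sponsor to decide.

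It is also fair that the composition is disclosed. The Synopsis labels arm B both control and placebo, and a careful reader can see the exchange of pectin for whey. But the title, the objectives and the planned analysis still speak of pectin against placebo, and disclosing the recipe does not change what those statements claim. An SAP, which is not at hand, might word the contrast more exactly. It could not separate the ingredients, and the protocol's own description would still need to agree with it.

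A reader might infer more than the documents support:
- **That the result is biased in a known direction or by a known amount.** The protocol gives no effect of whey on any endpoint. False-positive rates computed from an assumed whey effect, or weight differences computed from assumed energy values, would only reflect those assumptions.
- **That a positive result could say nothing in favour of pectin.** That goes too far. Extra whey would have to worsen the marker enough to account for the difference, and nothing in the protocol shows this.
- **That the product sheet shows whey to be active on these outcomes.** The line "Usual Daily Dose: 20-30g" places arm B at the top of the listed range and arm A below it, but it does not bear on inflammation or metabolism. Known Side Effects mentions whey beside pectin when excluding pregnant and breastfeeding women, but that concerns limited safety data only.

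**Conclusion.** The point holds as a mismatch between the contrast that the design delivers and the one that the protocol names. The arms differ by 15 g of whey a day, which is 12.9 g of protein a day or about 542 g over 42 bags on full adherence. This whey difference is inseparable from the pectin difference. The between-arm estimate is the effect of pectin in place of an equal weight of whey protein. Reading it as the effect of pectin against placebo requires the extra whey to have no effect on the outcomes, an assumption that the protocol neither states nor defends.

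The conclusion rests only on the stated bag contents, on which three sections agree, and on the product label. It does not depend on the sample size or on any assumed whey effect. It does not show that the estimate is biased towards either arm, or that the comparator is unacceptable.

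**What to change.** Leave the composition as the sponsor's decision and correct what the protocol says about it.

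1. In Statistics, Methods, and the Synopsis (Statistical methods), define the between-arm contrast as pectin in place of an equal weight of whey protein.
2. Describe arm B as a whey-protein control rather than a placebo wherever it appears: the title; the Synopsis entries for trial configuration, interventions, randomisation and statistical methods; the Placebo Arm heading in Details of Product(s); Trial / Study Configuration; Randomization and Blinding; Dietary intervention (6 weeks); Statistics, Methods; and the efficacy text under Secondary endpoint. Changing only some of these would leave the protocol inconsistent.
3. State that conclusions on the primary inflammatory markers, and on glucose, BMI, lipids, microbiome and CAP, are limited to that substitution.

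The cost is a protocol amendment of wording only, with no change to the bags, visits or data collection. The downside is a narrower claim: the trial would no longer say that it estimates the effect of pectin by itself.
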